# The impact of video gaming on cognitive functioning of people with schizophrenia (GAME-S): study protocol of a randomised controlled trial

**DOI:** 10.1186/s12888-020-03031-y

**Published:** 2021-01-18

**Keywords:** Gaming, Randomised controlled trial, Schizophrenia, Effectiveness

## Abstract

**Background:**

Video gaming is a promising intervention for cognitive and social impairment in patients with schizophrenia. A number of gaming interventions have been evaluated in small-scale studies with various patient groups, but studies on patients with schizophrenia remain scarce and rarely include the evaluation of both clinical and neurocognitive outcomes. In this study, we will test the effectiveness of two interventions with gaming elements to improve cognitive and clinical outcomes among persons with schizophrenia.

**Methods:**

The participants will be recruited from different outpatient units (e.g., outpatient psychiatric units, day hospitals, residential care homes). The controlled clinical trial will follow a three-arm parallel-group design: 1) cognitive training (experimental group, CogniFit), 2) entertainment gaming (active control group, SIMS 4), and 3) treatment as usual. The primary outcomes are working memory function at 3-month and 6-month follow-ups. The secondary outcomes are patients’ other cognitive and social functioning, the ability to experience pleasure, self-efficacy, and negative symptoms at 3-month and 6-month follow-ups. We will also test the effectiveness of gaming interventions on neurocognitive outcomes (EEG and 3 T MRI plus rs-fMRI) at a 3-month follow-up as an additional secondary outcome. Data will be collected in outpatient psychiatric services in Hong Kong. Participants will have a formal diagnosis of schizophrenia and be between 18 and 60 years old. We aim to have a total of 234 participants, randomly allocated to the three arms. A sub-sample of patients (*N* = 150) will be recruited to undergo an EEG. For neuroimaging assessment, patients will be randomly allocated to a subset of patients (*N*=126). We will estimate the efficacy of the interventions on the primary and secondary outcomes based on the intention-to-treat principle. Behavioural and EEG data will be analysed separately.

**Discussion:**

The study will characterise benefits of gaming on patients’ health and well-being, and contribute towards the development of new treatment approaches for patients with schizophrenia.

**Trial registration:**

ClinicalTrials.gov NCT03133143. Registered on April 28, 2017.

## Background

More than 21 million people worldwide suffer from schizophrenia [1]. Schizophrenia is associated with severe disabilities in cognition and global functioning [2, 3]. Deficits in attention, executive function and working memory are the core challenges for this patient group [4, 5]. Having a working memory is a crucial part of daily functioning and holding and manipulating information [6]. Poor working memory is associated with poor functional outcome [4] and limits for social relationships [7]. Disabling cognitive symptoms in schizophrenia are associated with prefrontal dysfunction [8].

Cognitive deficits can be improved with specialised cognitive training programmes. For example, remediation therapy is designed to improve attention, memory, and problem solving [9]. Various types of computer-based applications for cognitive remediation have also been established, as well as serious games, which are specialised for training cognitive deficits. Fisher et al. tested a set of computerised exercises in patients with schizophrenia and showed that those who made the most progress in the basic psychophysical auditory exercise also exhibited the most improvement in verbal working memory and global cognition [10]. More recently, video gaming in general (on a computer, console, online platform, or mobile device) and sole entertainment games (action, sport, role-playing, adventure, fighting, racing, family entertainment, casual games) [11] have opened up an avenue for new remedial interventions targeting attention, problem-solving, emotional expression, and socialization [12]. This approach is potentially more effective than direct instructional methods, such as coaching, which yields limited benefits for patients with schizophrenia [13]. Kühn et al., for example, reported that video gaming increases grey matter volume in the brains of healthy adults, and they recommended gaming for patients with schizophrenia [14].

Functional magnetic resonance imaging (fMRI) studies have recently been used in working memory tests for patients with schizophrenia [15]. Some studies have reported increased activation of the dorsolateral prefrontal cortex (DLPFC) in patients with schizophrenia during their working memory performance [16]. Imaging methods have also been used to assess the effectiveness of gaming interventions for neurocognitive outcomes. One fMRI study suggested that persons who have played a shooter game improved their attentional resources more efficiently than non-gamers [17]. A systematic review further suggests action video games as a promising method in mental health treatment, as asserting that specific types of video games can alter brain structure or improve certain aspects of cognitive functioning [18]. Video gaming may be particularly useful for persons who have difficulties in treatment compliance or engagement because gaming itself may offer positive experiences and emotions [19, 20], a sense of self-efficacy, relatedness, and social interaction [21, 22]. These effects are expected to benefit patients with schizophrenia [2–5]. Further, video gaming is cost effective and allows personalised targeting of specific brain abnormalities by ameliorating the dysfunction in specific brain circuits and normalizing network dynamics. When suitably scaled, gaming may be highly effective in countering the impact of risk factors associated with prodromal states of various mental disorders [14, 22]. This suggestion is in keeping with speculation that some commercially available video games may already have the potential to cause changes in human behaviour [23]. However, the influences of video gaming on brain function and structures, in relation to its potential benefits for cognitive functioning, social relationships [18], pleasure and self-efficacy, remains poorly characterised [13]. In addition, the most useful setting for the implementation of gaming interventions is still unclear [24].

We hypothesise that playing video games [13] may alter brain function, cognition and behaviour [23] for patients with schizophrenia [25]. Benefits for prospective memory impairments and emotion-behaviour decoupling related hedonia have been demonstrated in schizophrenia patients [26]. One neuroimaging study outside of the field of mental health shows that both early stimulus processing and late retention period activities associated with video gaming could improve visual working memory function, and suggests that video gaming might be suitable for patients with schizophrenia [27]. Indeed, there is some evidence that entertainment games can be useful in mental health in, for example, improving moods or stress levels [28, 29]. However, these are studies with small sample sizes and narrow scopes in age groups [30].

Based on the current role of video gaming [10], its rapid expansion in the market, and its promises in treatment for persons with schizophrenia, it is important to conduct a larger-scale investigation to fully characterise its potential clinical profile and efficacy [30]. Here, we will test the effectiveness of gaming embedded within two interventions in a longitudinal study on relevant cognitive and clinical outcomes, as well as EEG and neuroimaging assessments (structural MRI, resting-state fMRI, and diffusion tensor imaging) as a form of brain physiological readout.

## Methods

### Objectives

This study aims to compare the effectiveness of cognitive training using computerized gaming exercises to that of entertainment video gaming and a non-gaming, passive control group, looking at a range of outcomes. The primary objective is to test the effects of the interventions on patients’ cognition, especially on working memory at 3-month and 6-month follow-ups. The secondary objectives are to test the effects of the interventions on patients’ other cognitive and social functioning, the ability to experience pleasure, self-efficacy, and negative symptoms at 3-month and 6-month follow-ups. Additional secondary outcomes are EEG brain activity and structure related to working memory function at a 3-month follow-up.

### The hypotheses

Primary hypothesis:
Cognitive training with computerised exercises is more effective than entertainment video gaming or the non-gaming control in improving patients’ working memory at a 3-month and/or 6-month follow-up.

Secondary hypotheses:
2.Cognitive training with computerised exercises is more effective than entertainment video gaming and the non-gaming control in improving patients’ cognitive and social functioning, experience of pleasure, and self-efficacy at a 3-month and/or 6-month follow-up.3.Cognitive training with computerised exercises is more effective than entertainment video gaming and the non-gaming control in improving negative symptoms in schizophrenia at a 3-month and/or 6-month follow-up.4.Cognitive training with computerised exercises is more effective than entertainment video gaming and the non-gaming control in improving neurocognitive outcomes (EEG signals, brain activity and structure) at a 3-month follow-up.

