#### Secondary outcomes

##### Cognitive functioning

A battery of cognitive tests will be used to measure the processing speed [Trail Making Test, TMT, A [42]], attention and vigilance [Sustained Attention to Response Task, SART], visuospatial working memory [Spatial Span from WMS III [42]], and reasoning and problem solving [Wisconsin Card Sorting Test [42]]. The instruments to be used are well tested, reliable, recommended, and available in simplified/traditional Chinese, either in paper or digital format [42].

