##### Social functioning

A Chinese version of the Brief Social Phobia Scale, BSPS, will be used for assessing the severity of and treatment response to social phobia [43]. The Cronbach’s alpha for the Chinese version is 0.88, which states a high level of internal consistency [43].

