##### Experience of pleasure

The Temporal Experience of Pleasure Scale (TEPS, Chinese version) covers anticipatory and consummatory components (Cronbach’s alpha=0.83; test-retest reliability r=0.79) [44].

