In the main analysis, we will estimate and test efficacy of interventions on the primary and secondary outcomes. Based on the intention-to-treat principle, we will first assess intervention effects on the primary outcome, verbal working memory, by means of multilevel modelling analysis. A two-level model can be built with repeated time points at level 1, and patients at level 2. Two indicator variables, G2 and G3, will be included in the fixed part of the model to estimate and test mean differences between the cognitive training group with computerised exercises (G1) and the entertainment gaming group (G2), as well as between G1 and the non-gaming control group (G3). The baseline difference between G2 and G3 can be tested using a Ward test, based on the regression coefficient estimates of the two indicators. For changes in the outcome over time, two more indicators, variables T2 and T3, in contrast to the baseline time point, T1, will be included in the fixed part of the model to estimate changes from baseline to 3 months, and from baseline to 6 months. To assess the effects of interventions over time, interaction terms between the treatment group indicators, G2 and G3, and time indicators, T2 and T3, will be included in the fixed part of the model. The significantly different demographics between groups identified in the first step of the analysis and other possible confounders will be adjusted by including them in the main effect model. The within-patient random effects of the outcome measurements will naturally be taken into account by the level two variance in the model. A pairwise comparison and other hypotheses on the intervention effects can be tested using a generalised Ward test with an adequate degree of freedom from the modelling analysis. This analysis approach has two main advantages: a statistically highly efficiency and taking missing data into account. The effects of interventions on other secondary outcome measures, normally distributed and measured at three time points, such as patients’ cognitive and social functioning, experience of pleasure, and self-efficacy, will be analysed using the same model, but a separate model for each outcome. A multilevel logistic model will be used for outcomes in binary form, and multilevel multinomial models will be used for ordinal or nominal outcomes. For outcomes measured at two time points only, such as neurocognitive outcomes, the model will have only one time indicator with two interaction terms to test the efficacy of cognitive training with computerised exercises three months into the trial.

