
SPSS (the Statistical Package for the Social Sciences) Missing Values will be used to identify the amount and pattern of missing data. If missing values are few and randomly allocated, the last observation carried forward (LOCF) will be used to replace the missing data. If missing values are not randomly distributed, multiple imputation approaches will be used. A sensitivity analysis will be performed by comparing results from analysis datasets without missing data imputation and with imputation.

In all tests, significant differences between groups will be detected with a 95% confidence level, and *P* values of < 0.05 will be considered significant. Statistical analyses will be carried out with SAS System for Windows, version 9.4 (SAS Institute Inc.) or R statistical software (R Core Team, 2016).

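### The blanket P < 0.05 rule covers at least 32 secondary contrasts, and nothing states how they combine into a superiority claim, mainly for secondary hypothesis 2

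*Protocol article*

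**What the plan says.** All references are to the protocol article.

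- **The hypotheses.** Secondary hypothesis 2 says that cognitive training is "more effective than entertainment video gaming and the non-gaming control in improving patients’ cognitive and social functioning, experience of pleasure, and self-efficacy". Secondary hypothesis 3 makes the same comparison for "improving negative symptoms in schizophrenia at a 3-month and/or 6-month follow-up". Both join the two controls with *and*. The primary hypothesis joins them with *or*: "more effective than entertainment video gaming or the non-gaming control in improving patients’ working memory".
- **Secondary outcomes.** Eight scales are named. Four are cognitive ("A battery of cognitive tests will be used to measure the processing speed", followed by attention, visuospatial working memory and problem solving): TMT A, SART, Spatial Span and Wisconsin Card Sorting. The others are BSPS, TEPS, GSE and CAINS. TEPS "covers anticipatory and consummatory components", so eight is a minimum count of scores.
- **Cognitive and clinical outcomes (Data analysis).** The primary model has two group indicators, two time indicators and their interactions. The secondary scales "will be analysed using the same model, but a separate model for each outcome".
- **Same section, last paragraph.** "In all tests, significant differences between groups will be detected with a 95% confidence level, and *P* values of < 0.05 will be considered significant".
- **Power analysis and sample size.** The only multiplicity adjustment is here: four tests on the primary outcome, with the 5% level reduced to 0.01274.

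**The concern.** The secondary hypotheses are directional statements of superiority, and the significance rule is universal. Read together, they let any one of at least 32 contrasts be called significant at the unadjusted level. The article does not say whether one contrast is enough, whether both controls must be beaten on the same scale at the same visit, or how many scales hypothesis 2 needs. The primary outcome is analysed first, but nothing makes the secondary claims depend on its result.

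What is at stake is what the trial may conclude from its secondary scales. Four of the eight are cognitive tests, so a chance result on one of them could be reported as a significant cognitive benefit even if the primary working memory test showed none. The primary result itself is not affected.

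**Working it through.** **1. The plan's own adjustment.** For four primary tests, the Šidák level is 1 − (1 − 0.05)^(1/4) = 0.01274. Half of it is 0.0064, with z = 2.49, and 2(0.84 + 2.49)²/0.58² is about 66 per group. These match the article. It therefore recognises multiplicity for the primary outcome, but only in the sample size section.

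**2. Count of secondary tests.** 4 cognitive + BSPS + TEPS + GSE + CAINS = 8 scales. Per scale, 2 contrasts (against entertainment gaming and against non-gaming) × 2 follow-ups = 4. Total 8 × 4 = 32. Hypothesis 2 takes 7 scales (28 tests) and hypothesis 3 takes 1 scale (4 tests).

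**3. Expected chance findings with no true effect.** 32 × 0.05 = 1.6 in either direction, of which 32 × 0.025 = 0.8 favour cognitive training.

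**4. Bounds if all tests were independent.** At least one favourable result: 1 − 0.975^32 = 55.5%. This is too high, because the tests are correlated.

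**5. Simulation with correlation.** 200,000 replicates, three equal arms (the article allocates 1:1:1). The two contrasts share the cognitive training arm, which gives them a correlation of 0.5. Two inputs are assumptions, because the article does not give them: a correlation of 0.5 between the two follow-ups, and an equal correlation between scales of 0 to 0.8.

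| Event (8 scales, 2 times, each test two-sided 0.05) | 0 | 0.3 | 0.5 | 0.8 |
|---|---|---|---|---|
| Any of the 32 tests, either direction | 0.755 | 0.707 | 0.625 | 0.438 |
| At least one favouring cognitive training | 0.489 | 0.404 | 0.336 | 0.225 |
| Both controls beaten, same scale and time | 0.068 | 0.062 | 0.053 | 0.035 |
| Same, when one control is truly beaten on every scale and the other is not | 0.309 | 0.255 | 0.208 | 0.136 |

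Columns are the between-scale correlation. The first three rows assume no true effect anywhere. In the last row one contrast is taken as certain to succeed, so a false claim needs only a chance favourable result on the other. The independence bound for that row is 1 − 0.975^16 = 33%.

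Raising the between-time correlation to 0.7, with 0.5 between scales, changes little: 31% for at least one favourable result, 5.0% for both controls, and 19% for the last row.

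**6. Hypothesis 3 alone.** With one scale, both controls beaten at the same time has a chance of about 0.9% with no true effect. It is about 4.5% if one control is truly beaten (bound 1 − 0.975² = 4.9%).

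**The case against.** **Secondary multiplicity is usually left to the SAP.** The SAP is not shown, and this article condenses a fuller protocol. The absence of a hierarchy or an exploratory label is therefore not in itself an error, and that part of the objection stands. The article does, however, state a rule for all tests. An SAP that adjusted the secondary contrasts would contradict that sentence, so the sentence is a fair target.

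**The wording already asks for both controls.** Hypotheses 2 and 3 say *and* where the primary says *or*. Read literally, two controls do not multiply the chances, and the rate with no true effect is about 5%. This stands as a reading, but the analysis section never makes it a rule: it estimates the contrasts separately and applies the threshold to each. It also gives no protection over seven scales and two visits if only one control is truly beaten. That case is plausible here, since both gaming arms receive supervised sessions, usual care receives none, and the research assistants who collect follow-up outcomes are not masked.

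**Hypothesis 2 also joins its domains with *and*.** If every domain had to succeed against both controls at the same time, with any one of the four cognitive tests enough for cognition, the false claim rate would be at most about 0.15% with no true effect. It would be at most about 1.3% if one control were truly beaten. The article does not settle this reading either. A reader might infer that success on any mix of the seven scales is enough, but the text does not say so.

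**Other points that stand.** The primary outcome is assessed first, which is an order though not a gate. The plan also allows joint tests of several contrasts, so 32 separate claims are possible but not fixed. The Discussion is conditional in tone and does not announce efficacy claims from secondary scales.

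**Conclusion.** The concern holds in a limited form. The article fixes an unadjusted P < 0.05 for at least 32 secondary contrasts and leaves open what would count as meeting the hypotheses. With no true effect, the chance of at least one nominally significant result favouring cognitive training is about 34% (22-49%). With both controls required on the same scale at the same time, it is about 5% (3-7%), rising to about 21% (14-31%) if only one control is truly beaten on every scale. That last case is an upper-end scenario. All ranges rest on the assumed correlations.

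A reader might infer that a false secondary claim is likely, pointing to the 62% chance of any significant result (44-76%). The documents do not support this. That figure includes results against cognitive training, which cannot support either hypothesis. The favourable-direction rate stays below one half throughout, and the *and* wording lowers it much further if applied. Nor is the problem shared equally: it lies mainly with hypothesis 2, while hypothesis 3 carries about 0.9%, or 4.5% if one control is truly beaten.

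**What to change.** In the last paragraph of Cognitive and clinical outcomes:

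1. Limit the significance rule to the primary LNST analysis, at the adjusted level of 0.01274 already given in the sample size section.
2. State that a secondary superiority statement requires both controls to be beaten, as hypotheses 2 and 3 are worded, on the same scale at the same follow-up.
3. Report the secondary contrasts as exploratory, with estimates and 95% CIs.

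If the sponsor wants confirmatory secondary claims, a procedure gated on the primary result, with a fixed order or Holm over named scores and a named time, is an option. It is a choice, not a requirement.

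The change is a few sentences, made before unblinding, with no new data or participants. The downside is that some secondary results can no longer be called significant.

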### Trial design

The effectiveness of the intervention will be assessed using a controlled clinical trial with a pragmatic, three-arm parallel-group design. The three-arm design is chosen to explicitly test the superiority of the experimental cognitive training with computerised exercises (CogniFit) compared to the active control (entertainment games) and treatment as usual (non-gaming passive control) [31]. Since the objective of the study is to test the efficacy of the type of gaming (cognitive training with computerised exercises vs. entertainment gaming), having a three-arm trial is necessary to assess the effects of the gaming types separately.

To assess fidelity, we will use gaming diaries to verify whether the interventions have been delivered as intended (intervention fidelity) and confirm patient gaming activity (gaming frequency [number of gaming sessions per week], the length of each session [minutes], number of drop-outs). We will also analyse any information on the perceived strengths and limitations of interventions written in the patients’ diaries.

